### Sample size

As there are five primary endpoints (smoking, alcohol consumption, fruit intake, vegetable intake and physical activity) an alpha level of 0.01 will be used to adjust for the multiple comparisons. The prevalence of daily smoking in the control group at follow-up is expected to be 22 % [11]. We aim to recruit 1012 TAFE students at baseline (i.e., 506 per condition). Allowing for 20 % loss to follow-up at 6 months, data will be available for 405 participants per condition. With an expected intra-cluster correlation coefficient (ICC) of 0.005 this will give the study a design effect of approximately 1.04 and an effective sample size of 389 per group, which will provide 80 % power to find an absolute difference of 9.5 % (in daily smoking rates) between the groups at the follow-up visit. Allowing for a higher ICC for the continuous outcomes (0.01), the study will have 80 % power to detect an absolute difference of 0.25 SD in these measures at the 1 % significance level, which equates to a difference of approximately 1.25 standard drinks of alcohol, 0.25 pieces of fruit, 0.25 vegetables and 50 MET minutes of physical activity per week.

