### Statistical analysis

Descriptive statistics will be used to present baseline characteristics for the intervention and control groups. Logistic regression will be used to test if there is a statistically significant difference in the change in prevalence of daily smoking between the two treatment groups. The outcome in the model will be smoking status and the predictors will include time, group and an interaction term between time and group. The *p*-value associated with the interaction term will be used to determine if there was a statistically significant difference in change between the groups. Linear regression will be used to test if there was a statistically significant different change in the mean level of the other outcomes between the groups. The outcome in each model will be the participant’s value of the outcome measure post treatment and the predictors will include their baseline value and treatment group (i.e., Analysis of Covariance). The p-value associated with treatment group will be used to determine if there was a statistically significant difference in the change from baseline to follow-up between the groups. Both the logistic and linear regression models will also be fit within a Generalised Estimating Equation framework to adjust for the correlation of responses within classes. All analyses will be conducted according to the Intention To Treat principle and the approach suggested by White and colleagues will be used to handle missing data [47]. The initial analysis will include all available data and will be valid under the assumption that the missing data are missing completely at random. Sensitivity analyses will be conducted under different assumptions about the missing data mechanism.

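### Testing all five primary endpoints at a fixed 0.01 is valid, but Holm's step-down test would hold the same 5% familywise error and gain power when several endpoints respond

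*Protocol article*

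**What the plan says.** The Sample size section of the protocol article gives the reason for the adjustment, "As there are five primary endpoints (smoking, alcohol consumption, fruit intake, vegetable intake and physical activity", and then the rule: "an alpha level of 0.01 will be used to adjust for the multiple comparisons". The trial is sized on the same basis. For smoking, "The prevalence of daily smoking in the control group at follow-up is expected to be 22" per cent, and 80% power is claimed "to find an absolute difference of 9.5" percentage points with an effective 389 per group. For the other four endpoints, 80% power is claimed "to detect an absolute difference of 0.25 SD in these measures", "at the 1 % significance level".

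The Statistical analysis section decides each endpoint from one p-value. For smoking, the p-value "associated with the interaction term will be used to determine if there was a statistically significant difference in change between the groups". For the continuous outcomes, "The p-value associated with treatment group will be used to determine if there was a statistically significant difference". That section gives no threshold of its own and describes no stepwise rule. The article names neither a multiplicity method nor a 5% familywise level; both are implied by 0.05/5 = 0.01.

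**The concern.** A single-step rule holds every endpoint to 0.01 even after other endpoints have been rejected. Once one null hypothesis has been rejected, at most four can still be true if that rejection is correct, and 0.05/4 is enough for the next. A fixed 0.01 leaves that error allowance unused.

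This matters most when several endpoints respond. The intervention addresses all five behaviours together, and the Background reports that 98% of students have two or more of the risk behaviours. Several true effects are therefore a realistic case, although not a certain one. At stake is a real improvement with a p-value between 0.01 and 0.05 being declared non-significant although the familywise error rate did not require it.

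**Working it through.** **Inputs from the protocol article.** Five endpoints; alpha 0.01 each; 80% power; 22% daily smoking in controls and a 9.5-point difference (22% v 12.5%); 0.25 SD for continuous outcomes; 405 analysed per arm; 50 classes per arm; ICC 0.005 (smoking) and 0.01 (continuous).

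**Assumed, not in the article.** Two-sided tests; test statistics approximately normal; correlation between endpoints 0 or 0.3.

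**1. The plan's own figures reproduce.**
- Familywise level: 5 × 0.01 = 0.05. With independent endpoints and no true effects, 1 − 0.99⁵ = 4.9%.
- Smoking: class size 405/50 = 8.1; design effect 1 + 7.1 × 0.005 = 1.036, stated as about 1.04; 405/1.04 = 389. The two-proportion formula at two-sided 0.01 and 80% power gives 368 per group, or 389 with the continuity correction, which matches.
- Continuous: design effect 1 + 7.1 × 0.01 = 1.071; 405/1.071 = 378. Power = Φ(0.25 × √(378/2) − 2.576) = Φ(0.86) = 80.6%.

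So 80% power per endpoint at two-sided 0.01 is the right basis for the comparison.

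**2. The alternative.** Holm orders the p-values from smallest to largest and compares them in turn with 0.05/5 = 0.01, 0.05/4 = 0.0125, 0.05/3 = 0.0167, 0.05/2 = 0.025 and 0.05, stopping at the first failure. No threshold is below 0.01, so every Bonferroni rejection is kept. Control of familywise error needs no assumption about correlation.

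**3. Simulation at the design effects.** Each true effect has a z-statistic with mean 2.576 + 0.842 = 3.417 (unrounded inputs), which gives 80% power at 0.01. There were 1,000,000 replicates per scenario.

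| True effects | Average power, Bonferroni | Holm, corr. 0 | Holm, corr. 0.3 |
|---|---|---|---|
| 1 | 80.0% | 80.1% | 80.1% |
| 2 | 80.0% | 81.8% | 81.6% |
| 3 | 80.0% | 83.9% | 83.5% |
| 4 | 80.0% | 86.6% | 85.8% |
| 5 | 80.0% | 90.4% | 89.0% |

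- No Bonferroni rejection was lost in any replicate.
- The chance of at least one rejection was the same under both rules (for example 99.2% with three true effects, correlation 0), because Holm's first step is also 0.01.
- Holm's familywise error was at most 4.9%, reached when no endpoint has an effect. There it equals Bonferroni's. With some true effects it is higher than Bonferroni's but still below 5% (three true, correlation 0: 4.2% v 2.0%). The extra power comes from using this unspent allowance.

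**4. Effects half the design size.** The mean z-statistic is 1.709 and power at 0.01 is 19.3%. Average power under Holm is about 19.4% with one true effect and 21.5% (correlation 0) to 22.7% (correlation 0.3) with five. The gain is therefore about 0.1 to 3 points.

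**5. Decisions and intervals that disagree.** An endpoint rejected only at a later Holm step has p > 0.01, so a 99% interval from the same model includes no effect. At the design effects, at least one such result occurs in about 12–13% of trials with three true effects and 36–42% with five.

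**The case against.** The strongest reply is that nothing here is wrong. The article names its endpoints, fixes one threshold in advance and sizes the trial at it, and Bonferroni controls familywise error under any dependence. It also agrees exactly with 99% intervals, whereas every rejection that Holm adds conflicts with its 99% interval. A team may reasonably prefer that coherence. This stands, and it is why the point is a suggested improvement.

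A second reply is that the 0.01 appears under Sample size and the Statistical analysis section states no threshold, so an analysis plan that is not shown might already contain a step-down rule. This stands only in part: the sentence gives adjustment for multiple comparisons as the purpose of the 0.01, which reads most naturally as the testing rule too.

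A reader might go further and infer that Holm gives strictly more power at no cost. The figures do not support that. The chance of at least one rejection does not change, the gain with one true effect is about 0.1 point, and the mismatch with intervals is a real cost. A reader might also lead with the chance of detecting all five effects, which rises from 33% to 67% (correlation 0) or from 44% to 72% (correlation 0.3). But the article judges each endpoint separately and does not make success on all five its objective. That scenario also needs all five effects at full design size, including smoking falling from 22% to 12.5%, while the Background cites a trial that improved diet and activity with no effect on smoking cessation.

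**Conclusion.** The point holds as an inefficiency. The fixed 0.01 is valid Bonferroni control, and the documents do not support calling it a type I error fault. Holm at familywise 0.05 gives the same guarantee, loses no rejection and needs no more students. At the design effects it adds about 2 points of average power per true effect with two true effects, 3–4 with three, 6–7 with four and 9–10 with five. It adds almost nothing with one true effect, and about 0.1 to 3 points if all effects are half the design size. These sizes rest on two-sided testing, approximately normal test statistics, equal power for each true effect and correlations of 0 to 0.3. That Holm keeps every Bonferroni rejection and controls the 5% rate rests on none of the last three.

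**What to change.** Before outcome data are examined by group, add one sentence to the Statistical analysis section: the five primary p-values will be tested by Holm's procedure at a two-sided familywise level of 0.05, and Holm-adjusted p-values will be reported. With p-values ordered from smallest to largest, the adjusted value at rank i is the largest of (6 − j) × p at ranks j = 1 to i, capped at 1.

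Keep 0.01 in the Sample size section and describe it as Holm's first and strictest step; the sample size does not change. If 99% intervals are reported, label them as not matching the step-down decisions, since an endpoint rejected only at a later step will have an interval that includes no effect. The cost is this wording and that loss of correspondence. If the investigators value the correspondence more than the added power, keeping 0.01 throughout is defensible, and the article should then say so.

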### Ethics approval & trial registration

The University of Newcastle Human Research Ethics Committee has granted ethical approval for this cluster randomised trial (H-2014-0012). The trial is registered with the Australian New Zealand Clinical Trials Registry (ACTRN12615000105549).

## Discussion

This trial will be the first to target smoking, alcohol consumption, fruit and vegetable intake and physical activity in vocational education students using electronic feedback, online and telephone support. This trial will provide TAFE students with immediate electronic feedback and proactive referral to online and telephone services for each health behaviour that does not meet Australian health guidelines. Research has demonstrated that proactive enrolment into the NSW Quitline [26, 27] and the Get Healthy telephone service substantially increased service use [28]. This trial will extend this prior research by proactively and simultaneously offering online and telephone support for multiple health risk behaviours, an intervention with the potential to increase the population impact of these existing evidence-based services.

## Abbreviations

TAFE: Technical and Further Education
NSW: New South Wales
APEASE: Affordability, Practicability, Effectiveness and cost-effectiveness, Acceptability, Safety and Equity
ADIS: Alcohol Drug Information Service
THRIVE: Tertiary Health Research Intervention Via E-mail
GLTEQ: Godin Leisure Time Exercise Questionnaire
MET: Metabolic equivalent
BMI: Body Mass Index
ICC: Intra-cluster correlation coefficient
